## Abstract

**Introduction::**

The outbreak of novel coronavirus disease 2019 (COVID-19) has caused a global pandemic since December 2020. It has not only associated with physiological disorder but also with psychological distress and symptoms of mental illness. Whether the vaccines and antivirals can provide protects remains unknown. Traditional Chinese medicine (TCM) is recommended as an alternative and significant way of preventing and treating COVID-19 in China. However, few studies have assessed the benefits of this treatment and mental health after they recover. Our study is designed to investigate effects and safety when using TCM on the course of this disease and the impact of COVID-19 on pandemic-related anxiety.

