**Discussion::**

It will be the first prospective cohort study which uses *Baidu Jieduan Granule*, based on the innovation traditional Chinese medicine strategy of “ Internal and External Relieving -Truncated Torsion ” to treat the common type of COVID-19. The result of this study may provide evidence-based recommendations of TCM for treatment and psychological distress or symptoms of mental illness of the common type of COVID-19.

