### Objectives

2.2

The main aim of our trail is to investigate the efficacy and safety of *Baidu Jieduan Granule* in the common type of COVID-19 patients and assess mental health outcomes through our 1year follow-up.

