### Population

2.3

For this multicenter prospective cohort study, we will enroll 300 COVID-19 patients meeting the inclusion criteria from 4 medical centers. The recruitment duration will be lasted from February 2020 to June 2020; the follow-up will end on June 30, 2021. The study flowchart is as Figure 1.

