### Inclusion criteria

2.4

1.Patients diagnosed with COVID-19^[20]^1)Meeting one of the following evidences:1.Real-time reverse transcription-polymerase chain (RT-PCR) detection of new coronavirus nucleic acid shows positive.2.The tested virus gene is highly homologous to SARS-CoV-2.3.Serum SARS-CoV-2 lgM and lgG antibody are positive.4.Serum SARS-CoV-2 IgG antibody turns positive or the serum novel coronavirus specific IgG antibody in the recovery phase is 4 times or higher than that in the acute phase.2)Patient has the symptoms of cough, expectoration, chest pain, dyspnea, and fever.3)Imaging findings of pneumonia.2.18 years old ≤ age ≤80 years old;3.Informed consent, participate in this study voluntarily.

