### Grouping

2.8

Three hundred COVID-19 cases aged 18 to 80 years are assigned into 2 groups (experimental group and control group) basing on whether they use *Baidu Jieduan Granule* at a ratio of 1:1. The experimental group and the control group are paired with gender, age and basic diseases so that they are comparable.

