### Interventions

2.9

Patients in the experimental group use *Baidu Jieduan Granule* together with conventional Western medicine, while the control group accept standard Western medicine only. The *Baidu Jieduan Granule* comprises *Scutellariae Radix* (30 g), *Radix Rhei Et Rhizome* (15 g), *Gypsum Fibrosum* (45 g), *Cmnamomi Mmulus* (9 g), *Polygoni Cuspidati Rhizoma Et Radix* (30 g), *Verbenae Herb* (3 g), The *Baidu Jieduan Granule is* brownish yellow particles and provided by Beijing Kangrentang Pharmaceutical Co. LTD (Number: Jing 201800603), which is one of the biggest companies specializing in the production of Chinese medicine Granules.

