### Follow-up

2.11

After finishing the interventions of 2 weeks, telephone follow-up will be done on all patients for 1 year. We follow these patients on a monthly basis. If the patients were died, we will terminate our follow-up.

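### The abstract's aim of measuring the effect of COVID-19 on anxiety cannot be answered by this design, conflicts with the Objectives section, and the group comparison cannot support recommending TCM for psychological distress

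*Protocol article*

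**What the plan says.** The abstract's Introduction gives the study two purposes: the effects and safety of TCM, and "the impact of COVID-19 on pandemic-related anxiety". The abstract's Discussion then looks ahead: "The result of this study may provide evidence-based recommendations of TCM for treatment and psychological distress or symptoms of mental illness" in common-type COVID-19.

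The body words the mental-health purpose differently. Section 2.2 (Objectives) says the study will "assess mental health outcomes through our 1year follow-up", with no mention of an effect of COVID-19.

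On who is studied, section 2.3 states "we will enroll 300 COVID-19 patients meeting the inclusion criteria from 4 medical centers", and the first criterion in section 2.4 is "Patients diagnosed with COVID-19". On the comparison, section 2.8 says patients "are assigned into 2 groups (experimental group and control group) basing on whether they use" the granule; both groups receive Western medicine, "while the control group accept standard Western medicine only" (section 2.9).

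On timing, Table 1 (section 2.14) has one mark each for LSAs and DASS21, in the follow-up phase under the 1-year label, and none at D1, D3, D5, D7 or D14. Section 2.11 adds telephone follow-up: "We follow these patients on a monthly basis". It does not say whether the scales are given at those calls.

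**The concern.** An effect of COVID-19 on anxiety needs people without COVID-19, or the same people before they had it. The eligibility criteria, the grouping and the schedule provide neither. If the abstract's wording stands, the level of anxiety found at follow-up is likely to be reported as something COVID-19 caused, although it could equally have been there beforehand or reflect living through the pandemic without infection.

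The closing claim about TCM has a related weakness. It would rest on a difference in scores between patients who did and did not use the granule. Without a mental-health score at entry, such a difference may only show that the groups differed from the start.

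**Working it through.** The document gives no effect size, power or sample-size calculation for mental health, so there is no figure to reproduce. The check sets the aim beside what the design can supply.

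**1. Between-person contrast (infected v not infected).** Planned participants: 300 (section 2.3). Participants required to have COVID-19: 300 (section 2.4). Uninfected participants: 300 − 300 = 0. The control group in section 2.9 is also made up of COVID-19 patients, so it is a comparator for the granule and not for infection.

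**2. Within-person contrast (before v after).** Scale scores before illness: 0. Scale scores at D1 to D14 in Table 1: 0. A score on D1 would in any case have been taken during acute illness, so it would not be a pre-infection value. The position of the marks in Table 1 seems reliable: the single mark for clinical outcomes falls under D14, as one would expect.

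**3. Does the monthly contact rescue the aim?** Suppose the scales were given at every monthly call. All those scores would come after the two-week intervention, and none would come from an uninfected person. They would describe a course after recovery. The counts in steps 1 and 2 would stay at 0.

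**4. What section 2.2 needs.** Assessing mental health outcomes over the year requires only scores in recovered patients. Table 1 supplies these. This objective can be met, so the abstract and the Objectives section state different aims and the design fits only the second.

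**5. What the group difference can show.** The observed difference in scores is the sum of:
- any effect of the granule;
- differences in mental health that existed at entry;
- differences in other characteristics linked to granule use;
- differences in who survives and can be reached, since follow-up ends at death (section 2.11).

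The plan deals with part of this. Section 2.8 pairs on gender, age and underlying disease. Section 2.5 excludes severe mental illness, which leaves mild or moderate anxiety or depression free to differ between groups. Section 2.12 describes t-tests, nonparametric tests and chi-squared tests, none adjusted, and names a logistic method only for survival. With no entry score on either scale, the second component can be neither measured nor removed.

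**The case against.** The strongest reply is that the abstract phrase is loose wording and the study's real aim is in section 2.2. The abstract's Method paragraph, the end of the Introduction and section 3 describe the mental-health part in similarly descriptive terms. This largely stands. A reader might infer that the mental-health part of the study has no answerable question at all. The documents do not support that, because the descriptive objective is answerable. What remains is that the abstract states a causal aim that neither section 2.2 nor the design carries.

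A reader might also infer from Table 1 that each scale is given only once. That is not established. The 1-year label and the marks sit in the middle of a five-column follow-up block, so the label may cover the whole phase, and section 2.11 provides for monthly contact. The point here does not depend on it.

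Third, the authors list the lack of randomisation as a limitation in section 3, they pair the groups, and they say only that results may provide recommendations. These are fair mitigations. But the listed limitations do not mention the missing baseline score or the missing uninfected comparator, and pairing on three factors does not replace a mental-health score.

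Finally, an article condenses a fuller protocol. The conflict does not come from omission: eligibility, grouping and schedule are all stated, and they are at odds with the stated aim.

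**Conclusion.** The concern holds for the abstract's aim and for its closing claim, and not for the objective in section 2.2. With 0 uninfected participants and 0 scale scores before or during the 14-day treatment period, the effect of COVID-19 on anxiety cannot be identified, whatever the sample size or the number of follow-up scores. Precision is not the issue.

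The granule-versus-control difference can be reported as an exploratory association among survivors reached at follow-up. It cannot carry a recommendation of TCM for psychological distress.

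The conclusion assumes that Table 1 shows the full schedule for D1 to D14 and that the tests in section 2.12 are those intended for the mental-health scores. A separate analysis plan with covariate adjustment would ease the second part but would not supply the missing baseline score. Mental health is part of the main aim but not of the primary outcome (section 2.10.1), so this limits what may be concluded about mental health and leaves the primary outcome untouched.

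**What to change.** 1. Align the abstract's aim with section 2.2, for example: to describe social anxiety, depression, anxiety and stress after COVID-19 in survivors reached at follow-up, and to compare them between groups as an exploratory association adjusted for covariates recorded at D1.
2. Remove the reference to the impact of COVID-19, and the claim about TCM recommendations for psychological distress or mental illness.
3. In the analysis, adjust for D1 variables that Table 1 already schedules, such as demographics, general condition, primary disease, complications and APACHE II.
4. Add the missing baseline mental-health score and the missing uninfected comparator to the limitations in section 3.
5. State whether the scales are given at the monthly calls.

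A DASS21 score from a later call should not be used as an adjustment covariate. All calls follow the two-week intervention, so such a score is post-treatment; adjusting for it could bias the group comparison and would not replace a baseline.

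The cost is rewording and a regression on data already planned, with no new data collection. This matters because section 4.1 says the trial is already in follow-up. The downside is a weaker claim.

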**Method::**

For this prospective cohort study, we will enroll 300 COVID-19 patients aged 18 to 80 years at 4 centers. We divide them into 2 groups, according to whether they use *Baidu Jieduan Granule* at a ratio of 1:1. We will compare treatments combined *Baidu Jieduan Granule* with conventional Western medicine (experimental group) vs treatment of conventional Western medicine only (control group). The basic information of patients including demographic, general condition, primary diseases, and complications will be assessed. Related examines will be conducted at 1, 3, 5, 7, and 14 days. The primary outcomes are clinical outcome. A follow-up time of 1 year (to June 30, 2021) allow us to evaluate the psychiatric disorder after recovery. We will monitor adverse events throughout the trial.

**Discussion::**

It will be the first prospective cohort study which uses *Baidu Jieduan Granule*, based on the innovation traditional Chinese medicine strategy of “ Internal and External Relieving -Truncated Torsion ” to treat the common type of COVID-19. The result of this study may provide evidence-based recommendations of TCM for treatment and psychological distress or symptoms of mental illness of the common type of COVID-19.

## Introduction

1

Since December 2019, patients with pneumonia-like symptoms of unknown origin was found 1 after other in Wuhan city, Hubei Province.^[1,2]^ Soon after the outbreak, researchers obtained the whole genome sequence by sequencing from the patients samples, and the result revealed that it was a novel coronavirus (COVID-19).^[1]^ The International Committee on Taxonomy of Viruses (ICTV) named the virus as severe acute respiratory syndrome coronavirus 2 (SARS-CoV-2). This kind of virus spread quickly between humans, leading to a worldwide pandemic. As of May 20, 2020, more than 4.7 million people across 215 countries or territories have been infected, of which more than 316 000 cases died.^[3]^ In February 2020, the WHO (World Health Organization) declared the outbreak as the public health emergency of international concern (PHEIC) for the situation getting worse and worse.^[4]^ Therefore, how to prevent and cure this kind of new infectious disease is of high significance.

Analyzing some retrospective studies of COVID -19 cases,^[5,6]^ the commonest manifestations were respiratory and digestive symptoms. Those severe patients could rapidly progress to acute respiratory distress syndrome, septic shock, refractory metabolic acidosis, and coagulation dysfunction, resulting in life-threatening. Currently, there is no specific medicine for the treatment of COVID-19. As we know, most antiviral drugs undergoing clinical testing in patients with COVID-19 are originally developed against influenza, HIV, Ebola, SARS, and MERS.^[7,8]^ But their effects and safety remain unknown. Furthermore, some findings suggest that psychiatric complications for people affected by COVID-19 are universal including post-traumatic stress symptoms (PTSS)/post-traumatic stress disorder (PTSD), anxiety and depression. Experts point out the need to pay specific attention to them at risk of further distress that may need tailored interventions.^[9]^

“Internal and External Relieving -Truncated Torsion” strategy means in the very beginning of COVID-19, we use TCM which can release the exterior (sweating) or dredging the interior (draining and defecating) to intervene timely so that we can remove pathogenic factors, treat diseases and then prevent common type COVID-19 patients from developing into severe and critical illnesses. This theory originates from the idea of “ preventive treatment of disease” in “ *Inner Canon of Yellow Emperor*”. In the long-term struggling against hundreds of thousands of times of infectious disease outbreak, this theory gradually got improved and perfected. Wu Youke, the most famous expert of contagious disease in Ming Dynasty, proposed that the pathogenic factors should be eliminated as soon as possible in his book “*Plague Theory*”.^[10]^ Ye Tianshi, another great medical expert, also put forward the viewpoint of protecting the organs which are not attacked first in “*Treatise on Epidemic Febrile Diseases*”.^[11]^

The main components of *Baidu Jieduan Granule* are *Cmnamomi Mmulus* which can promote sweating, *Radix Rhei Et Rhizome* and *Gypsum Fibrosum* both of which can dredge the interior. We also add some other components with heat-clearing and antiviral effects considering the features of COVID-19. Among them, *Cmnamomi Mmulus*, *Radix Rhei Et Rhizome* and *Gypsum Fibrosum* have shown sound clinical results in the treatment of viral and bacterial pneumonia for more than 10 years.^[12,13]^ Since January 2020, *Baidu Jieduan Granule* has been applying in hospitals in Wuhan and other epidemic areas in Hubei province to cure COVID-19 or some suspicious patients with respiratory infection symptoms. Combining the data from these studies and data from previous, it demonstrated that *Baidu Jieduan Granule* is of great effects and high safety. Moreover, modern pharmacological studies have proved that *Radix Rhei Et Rhizome* has the function of antibacterial and antivirus, for example, streptococcus A, streptococcus B, Streptococcus pneumonia, staphylococcus aureus, influenza virus A and influenza virus B. It can also significantly reduce the levels of TNF-α, IL-2, IL-6, IL-8 and other inflammatory cytokines in patients with systemic inflammatory response syndrome (SIRS), inhibit the excessive inflammatory reaction and maintain immune stability.^[14]^ In primary studies, *Cmnamomi Mmulus* plays an immunosuppressive role by inhibiting the proliferation of spleen cells.^[15]^ Cinnamyl alcohol can alleviate airway and lung inflammation by reducing the release of inflammatory factors and cytokines.^[16]^*Gypsum Fibrosum* is composed of 2 layers of silica tetrahedron and 1 layer of magnesium oxide octahedron.^[17]^ The surface adsorption capacity and electrostatic adsorption capacity of *Gypsum Fibrosum* can fix the virus and its toxin on the mucosal surface of the small intestine, making it lose the ability to cause disease.^[18,19]^

In this multicenter, prospective cohort study, we aim to use the *Baidu Jieduan Granule* combined with Western medicine to dynamically observe the changes of patient's blood, cytokines, coagulation function, chest computed tomography (CT), respiratory distress (respiratory rate, RR), blood oxygen saturation, oxygenation index, and patient prognosis (healing, worsening, and death),to prove the clinical efficacy of *Baidu Jieduan Granule* in curing COVID-19, to reveal the possible mechanism from the immune route, and to evaluate the safety. We will also assess mental health outcomes through our 1 year follow-up.

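### The pairing said to make the two groups comparable omits time since symptom onset, which entry does not limit, so an illness-day difference between groups would bias the D14 recovery comparison

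*Protocol article*

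**What the plan says.** **Rationale (Introduction).** The "strategy means in the very beginning of COVID-19, we use TCM which can release the exterior (sweating) or dredging the interior", with the aim to "prevent common type COVID-19 patients from developing into severe and critical illnesses".

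**Entry (2.4 and 2.5).** Laboratory proof of infection is by "Meeting one of the following evidences", a list of four. The fourth reads: "Serum SARS-CoV-2 IgG antibody turns positive or the serum novel coronavirus specific IgG antibody in the recovery phase is 4 times or higher" than the acute-phase level. Two further items stand beside the laboratory proof: "Patient has the symptoms of cough, expectoration, chest pain, dyspnea, and fever" and "Imaging findings of pneumonia". No inclusion or exclusion criterion sets a maximum time from onset or from diagnosis.

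**Groups (2.8).** Patients fall into the two groups according to whether they use the granule, 1:1. On comparability: "The experimental group and the control group are paired with gender, age and basic diseases so that they are comparable". The Discussion lists the lack of randomisation as a limitation and does not mention illness day.

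**Outcome and analysis (2.10.1, Table 1, 2.12).** Clinical outcomes have a single mark in Table 1, at D14. Patients in each category are counted and expressed as ratios. Rates are compared by chi-squared at P < .05. Logistic analysis is mentioned only for survival, and no covariate is named for any comparison.

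**The concern.** Recovery under 2.10.1 needs a normal temperature for three days, complete loss of respiratory symptoms and two negative nucleic acid tests. If these tend to arrive with time since onset, a patient further into the illness at D1 is more likely to meet them by D14, whatever the treatment. Study day and illness day are not tied together by the entry criteria. A patient entering on illness day 3 may therefore be paired with one entering on day 12, and both are read at the same study day.

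In a randomised trial this would add noise. Here use of the granule defines the group, so illness day at D1 could differ systematically between groups. The stated pairing would not correct that, and neither would the stated chi-squared test. What is at stake is whether a difference in the primary outcome can be read as an effect of the granule.

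**Working it through.** **1. The plan's own figures.** There is no power calculation to reproduce (2.7). The count is consistent: 4 centres × 75 = 300. With the supposed 10% withdrawal, 300 × 0.90 = 270, or 135 per group if losses are equal.

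**2. Inputs that are assumed, not documented.** Time T from onset to full recovery is normal with mean 20 days and SD 6, the drug has no effect, and nobody has recovered at entry. D1 falls on illness day e, so D14 falls on day e + 13. For simplicity, everyone in a group shares the same e.

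**3. Recovery by D14 for entry on illness day e.**

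P(T ≤ e + 13 | T > e) = [Φ((e + 13 − 20)/6) − Φ((e − 20)/6)] / [1 − Φ((e − 20)/6)]

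| Entry day e | Φ at D14 | Φ at entry | Recovered by D14 |
|---|---|---|---|
| 3 | 0.2525 | 0.0023 | 0.251 |
| 6 | 0.4338 | 0.0098 | 0.428 |
| 8 | 0.5662 | 0.0228 | 0.556 |
| 12 | 0.7977 | 0.0912 | 0.777 |

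**4. False difference from a 2-day gap.** Day 8 minus day 6: 0.556 − 0.428 = 0.128, about 13 points. Over other assumed values:

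| Mean | SD 4 | SD 6 | SD 8 |
|---|---|---|---|
| 16 | 0.120 | 0.101 | 0.079 |
| 20 | 0.197 | 0.128 | 0.090 |
| 24 | 0.121 | 0.105 | 0.082 |

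The range is 8 to 20 points.

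**5. What the planned test would do with it.** Take 135 per group, proportions 0.556 and 0.428, and a two-sided 5% level (sidedness is not stated in 2.12). The null standard error is √(2 × 0.492 × 0.508 / 135) = 0.0609, so the critical difference is 1.96 × 0.0609 = 0.119. The standard error under the assumed proportions is √((0.556 × 0.444 + 0.428 × 0.572)/135) = 0.0604. The probability of exceeding 0.119 when the expected difference is 0.128 is about 56%, for an inert drug.

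**6. A second model, to see how far this depends on the first.** Split entrants into early and late, with assumed D14 recovery of 50% and 80%, no drug effect, and a late share of 30% in controls. Recovery in a group = late share × 0.80 + (1 − late share) × 0.50.

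| Late share, granule group | Granule | Control | False difference | Rejection, 135 per group |
|---|---|---|---|---|
| 30% | 0.59 | 0.59 | 0 | 5% |
| 40% | 0.62 | 0.59 | 3 points | 8% |
| 50% | 0.65 | 0.59 | 6 points | 17% |
| 60% | 0.68 | 0.59 | 9 points | 34% |
| 70% | 0.71 | 0.59 | 12 points | 54% |

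The first row matters as much as the rest: with illness day balanced, the error rate stays at 5%.

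**The case against.** **The early-treatment text is rationale, not the objective.** A reader might infer that the trial fails to test its own strategy. The documents do not support that. Objectives (2.2) ask about efficacy and safety in common-type patients, without limiting the question to early illness. Late entrants may dilute an effect confined to early treatment, but enrolling them does not contradict the stated aim.

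**The serology route proves little.** A reader might take "specific IgG antibody in the recovery phase is 4 times or higher than that in the acute phase" to mean that convalescent patients are enrolled. That wording is one limb of one of four alternative proofs; the other limb is IgG turning positive. Symptoms and pneumonia on imaging are listed alongside. Nothing shows that anyone entered this way. The point rests on the missing limit, not on serology.

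**Onset date may be collected.** Table 1 lists categories of assessment, and the case report form (Additional file 5) is not shown. Its absence from Table 1 is therefore no evidence that the date is unrecorded.

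**Adjustment may be in an analysis plan.** This stands as a possibility. The article nevertheless names its three pairing variables, asserts comparability from them, and names an unadjusted test.

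**The size is invented, and this is ordinary confounding.** The first half is right: recovery times, the 2-day gap and the assumption that recovery becomes likelier with illness day are not in the documents, and no statement suggests that users enter earlier or later. The second half is also fair, and non-randomisation is acknowledged. But a general caveat does not replace control of a specific, retrievable variable tied directly to a fixed-day recovery outcome.

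**Conclusion.** The point holds as a conditional one. Entry does not limit time since onset, the pairing omits it, and the primary outcome is a single reading at a fixed study day compared without a named covariate. The claim of comparability in 2.8 is therefore stronger than its three variables can carry. If illness day at D1 differs between groups, the recovery ratio is biased. A 2-day gap would give about 8 to 20 points under the assumed recovery times (mean 16 to 24 days, SD 4 to 8). These figures show that a modest gap could matter; they do not estimate the actual bias, whose existence, direction and size the documents leave open.

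Nor do the documents support making an early-entry subset the main comparison. That would narrow the objective in 2.2 and shrink a sample that has no power basis. The point is a worthwhile, inexpensive improvement to the comparison.

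**What to change.** 1. Take the symptom-onset date for every patient from the hospital record or case report form, and compute days from onset to D1.
2. Report its distribution by group, so that readers can see whether a gap exists.
3. Adjust the D14 comparison for it, for example by logistic regression for recovery with days from onset and the pairing variables (gender, age, basic diseases). Alternatively, add it to the pairing. Recruitment was due to end in June 2020 and the trial is reported as in follow-up, so adjustment is the easier route: re-pairing may discard patients from sets already formed.
4. Fix the model and the handling of unknown onset dates before outcomes are compared.
5. Report results by time since onset as a secondary analysis, because the rationale concerns early treatment. Any entry window is for the investigators to decide.

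Cost: one data item per patient where it is not already held, slightly more analysis work, and a rule for patients whose onset date cannot be found. No new patients or procedures are needed.
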